### Sample Size

As recommended in the literature [24], a precision-based approach (ie, 95% CI width) was used to determine the sample size. Using a custom R script (R Foundation for Statistical Computing) developed by Muñoz Laguna et al [15] for a similar study [16], it was estimated that a sample size of ~25 participants per arm would yield Bang BI 95% CI widths of 0.45. Allowing for ~15% loss to follow-up, we computed an adjusted sample size of ~30 participants per arm (ie, 25/[1.0‐0.15]=~30).

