### Measurements (All Assessments Will Be Performed by the Data Team)

#### Primary Outcome

Blinding will be assessed immediately following each session and directly prior to the second session via a brief electronic survey whereby participants will be asked (1) their perceived group allocation (“genuine adjustments,” “sham adjustments,” and “I don’t know”), (2) if their group assignment was revealed to them in any way (“No,” “Yes - explain”), (3) if they felt any changes in their body following their sessions (“No,” “Yes-explain,” and “I don’t know”), and (4) if they have received chiropractic care prior to this study (“No” and “Yes-for how long-what kind”). This data will be stored in Jotform. The Bang BI is a continuous value from −1 to 1 computed on each trial arm [22]. Per the index developers, an index score of 1 indicates that all responses are correct, suggesting complete unblinding. An index of −1 denotes that all responses are incorrect, suggesting either complete blinding or unblinding in the opposite direction if participants have some bias leading them to believe they are in the opposite arm. An index of 0 indicates half of the responses are correct and half are incorrect, which suggests random guessing. Arm-level Bang BIs between −0.3 and 0.3 are commonly interpreted as “successful blinding” [14-16]. Successful blinding might also be inferred in cases of “wishful thinking,” whereby trial participants tend to believe they received genuine treatment irrespective of group assignment, resulting in Bang BIs for the genuine and sham groups approaching 1 and −1, respectively (summed Bang BI ≈0) [23].

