### Comparison to Prior Work

This multisession trial is the second step in our lab’s quest to develop a standardized sham protocol. Previously, a feasibility study was conducted in our lab that assessed blinding success following a single session of the same sham and genuine chiropractic techniques mentioned in this protocol. Bang BI point estimates suggested a high level of unblinding in the genuine group but successful blinding in the sham, both immediately posttreatment as well as 48 hours later. We hypothesize similar results from this study.

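### The single Bang BI interval width of 0.45 at 25 per arm overstates precision for a sham arm blinded within ±0.3, unless most participants answer don't know

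*Protocol article*

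**What the plan says.** The Sample Size section says that "a precision-based approach (ie, 95% CI width) was used to determine the sample size", and reports that "it was estimated that a sample size of ~25 participants per arm would yield Bang BI 95% CI widths of 0.45". The figure is attributed to an R script from a similar study. The section then inflates the number: "Allowing for ~15% loss to follow-up", "we computed an adjusted sample size of ~30 participants per arm". It gives no assumed index value, no assumed share of don't-know answers and no separate figure for each arm.

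The Primary Outcome section describes a three-answer question on "their perceived group allocation (“genuine adjustments,” “sham adjustments,” and “I don’t know" and says that "The Bang BI is a continuous value from −1 to 1 computed on each trial arm". It adds that "Arm-level Bang BIs between −0.3 and 0.3 are commonly interpreted as" successful blinding. It also allows that success might be inferred from wishful thinking, with the genuine arm near 1 and the sham arm near −1.

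Comparison to Prior Work reports from the feasibility study that "Bang BI point estimates suggested a high level of unblinding in the genuine group but successful blinding in the sham", and hypothesises similar results here. No numerical index is given for either arm.

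**The concern.** The width of a Bang BI interval is not a function of n alone. It is widest when guesses are evenly split and few people answer don't know. It is narrowest when nearly everyone guesses the same way or nearly everyone answers don't know. One unconditional width for both arms therefore sits badly with a hypothesis that the arms will behave differently, one strongly unblinded and the other blinded.

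Precision is the only stated basis for the sample size, and the credibility of the sham is the main aim of the trial. The primary analysis is a point estimate with a 95% interval in each arm. If 0.45 fits only unusual response patterns, readers will expect a sharper answer about the sham arm than 25 participants can give.

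**Working it through.** **Inputs.** From Sample Size: 95% level, n = 25 evaluable per arm, stated width 0.45, 15% loss, 30 per arm after inflation. From Primary Outcome: three answer categories, an index from −1 to 1, and a band of ±0.3. The article does not state the index value, the don't-know share or the type of interval. I therefore vary the first two and assume the usual large-sample (multinomial) variance.

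**The plan's own figures.** The inflation step reproduces: 25/0.85 = 29.4, rounded up to 30. The 0.45 cannot be reproduced directly because its inputs are not given, so I solve for the inputs that would produce it.

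**Formula.** Let d be the don't-know share and BI the correct share minus the incorrect share. Then

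variance = (1 − d − BI²)/n, and width = 2 × 1.96 × √[(1 − d − BI²)/n].

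**What 0.45 requires at n = 25.** 1 − d − BI² = 25 × (0.45/3.92)² = 0.329. Hence:

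- BI = 0: d = 1 − 0.329 = 0.67.
- BI = ±0.3: d = 1 − 0.09 − 0.329 = 0.58.
- d = 0: BI = ±√(1 − 0.329) = ±0.82, meaning about 91% guess the same way.

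**Widths inside the ±0.3 band.**

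| Don't-know share | n = 25, BI = 0 | n = 25, BI = ±0.3 | n = 30, BI = 0 |
|---|---|---|---|
| 0% | 0.78 | 0.75 | 0.72 |
| 20% | 0.70 | 0.66 | 0.64 |
| 40% | 0.61 | 0.56 | 0.55 |
| 50% | 0.55 | 0.50 | 0.51 |
| 60% | 0.50 | 0.44 | 0.45 |
| 67% | 0.45 | 0.38 | 0.41 |

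**Widths for a one-sided arm at n = 25.** At BI = ±0.8 the width is 0.47 with no don't-know answers and 0.40 with 10%.

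**Can both arms share one width?** Take a genuine arm at BI = 0.8 with d = 0, so that 1 − 0.64 = 0.36. A sham arm at BI = 0 matches it only if 1 − d = 0.36, that is, 64% don't-know answers.

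**Other readings of 0.45.**

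- A 90% interval at BI = 0 gives 0.51–0.66 for 0–40% don't-know answers.
- A half-width of 0.45 is impossible at n = 25, because the largest possible half-width is 0.784/2 = 0.39.
- Simulated mean realised widths at BI = 0 and n = 25 are 0.77, 0.69 and 0.59 for 0%, 20% and 40% don't-know answers, close to the formula.

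None of these recovers 0.45 for an arm near 0 with up to 40% don't-know answers.

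**Scale of the gap.** A width of 0.45 at BI = 0 would need (3.92/0.45)² × (1 − d) evaluable participants per arm: 76 at d = 0, 61 at d = 20% and 46 at d = 40%.

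**The case against.** The best defence is that the figure comes from a script we cannot see, and that a journal article may leave scenario inputs to a fuller document. A reader might infer that the script or its use contains an arithmetic slip. The documents do not show that. What they show is a conditional figure stated without its condition. The point therefore concerns a number the article does state, and would stand even if the inputs are recorded elsewhere.

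A second defence is that 0.45 can be met in an arm that counts as blinded, and this is correct. It is reached inside the ±0.3 band when don't-know answers are the majority. It is also reached in a sham arm near −0.82, which the Primary Outcome section says might count as success through wishful thinking. If both arms lay near ±0.82 with no don't-know answers, both widths would be 0.45. So it would be wrong to say that no blinded arm can attain the stated width.

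A reader might also infer that the trial fails unless the sham interval lies wholly inside ±0.3. The article sets no such rule: it applies the band to the index and promises an estimate with an interval. Nor is there a single don't-know share below which the interval exceeds the 0.6-wide band. That share is about 41% at BI = 0 (1 − 0.586) and about 32% at ±0.3 (1 − 0.09 − 0.586).

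Finally, the realised interval will show the true precision whatever was planned. That limits the harm, but it does not justify the planning statement.

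**Conclusion.** The concern holds in a bounded form. As stated, 0.45 is too favourable for a sham arm blinded in the ±0.3 sense unless most participants answer don't know. With 0–40% don't-know answers and 25 evaluable, the width is about 0.61–0.78 at BI = 0 and 0.56–0.75 at ±0.3, roughly 1.2 to 1.7 times the stated figure (0.56/0.45 to 0.78/0.45). Evaluating all 30 narrows the range at BI = 0 only to 0.55–0.72. The figure suits a strongly one-sided arm, which is closer to what is hypothesised for the genuine arm.

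This rests on the large-sample variance and on don't-know shares chosen to span a range, since the article gives neither the expected index nor the expected share. The article does not name its interval method, so no conclusion is drawn about that method's coverage.

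**What to change.** Keep N = 60. In Sample Size, replace the single 0.45 with an expected width for each arm, and state the index value and don't-know share assumed for each. For example, with 25 evaluable per arm the 95% width is about 0.6–0.8 for an arm with an index near 0 and 0–40% don't-know answers, and about 0.4–0.5 for an arm near ±0.8 with 0–10% don't-know answers. If the script assumed a particular response distribution, report it.

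In the primary analysis text, say that the sham-arm estimate will be interpreted in the light of that precision.

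The change is one of wording, needs no extra participants and can be made before the analysis. Its only downside is a less favourable stated precision.

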### Statistical Considerations (Primary Outcome)

The primary focus will be on arm-specific blinding, which will be reported using Bang BI point estimates and 95% CIs computed using a custom script written in “R” (v4.4.3) [25], which incorporates the “BI” package [26].

### Statistical Considerations (Secondary Outcomes)

As our sample size determination was based on our primary outcome (ie, Bang BI), estimates derived from secondary end points will be considered exploratory and interpreted with caution. Additionally, to guard against over-interpretation of results, we will only perform estimation and not perform null hypothesis significance testing. James BI point estimates and 95% CIs will be constructed using a custom R script incorporating the “BI” package. For group-level analysis of other secondary outcomes, mixed models will be run via custom R scripts incorporating the lme4 package [27]. Mixed models account for nonindependent data (eg, repeated measures) and have been shown to provide robust estimates in longitudinal designs even with high levels of missing data [28]. Between-group change score differences over time will be evaluated using linear mixed models with random intercepts adjusting for age, sex, and baseline values.

$$\text{lmm}=\text{lmer}\;\left(y-y_{\text{baseline}}∼1+\text{time}*\text{group}+y_{\text{baseline}}+\text{age}+\text{sex}+(1|\text{ID}),\;\text{data}=d\right)$$

Assumption checks will be performed via “visualize()” in the flexplot package [29,30]. If model assumptions are severely violated, data were evaluated via generalized linear mixed models incorporating a gamma distribution and a log link.

$$\text{glmm}=\text{glmer}\;\left(y-y_{\text{baseline}}∼1+\text{time}*\text{group}+y_{\text{baseline}}+\text{age}+\text{sex}+(1|\text{ID}),\;\text{data}=d,\;\text{family}=\Gamma (\text{link}=\log)\right)$$

Between-group change score difference point estimates and 95% CIs will be computed and plotted using the emmeans package [31]. Gait parameters include multiple correlated measures. Therefore, Bonferroni correction will be applied to account for multiplicity and control the family-wise type I error rate.

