### Participant Timeline

This trial will require 2 sessions, one week apart. The participants will receive the same intervention (ie, genuine or sham SMT) at both sessions. The study flow is outlined in Figure 1.

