### Assessments

Participants will be asked to attend 2 separate sessions approximately one week apart. Automated text reminders will also be sent via ChiroHD software (ChiroHD Inc) ~24 hours and~3 hours prior to each session.

To assess gait, participants will be asked to walk on a motorized treadmill at their preferred walking speed (PWS). Participants will be fitted with 16 inertial measurement units at different anatomical landmarks. Inertial measurement units will then be calibrated using commercial motion-capture equipment (NORAXON MyoMotion, MR2; Noraxon Inc). Participants will be fitted with a pair of slip-resistant socks prior to testing. They will then be instructed to step onto the nonmoving treadmill to begin the PWS assessment. Participants will start by walking on the treadmill at a speed of 0.5 mph. A trained research investigator will then increase the speed by 0.1 mph increments every 2‐4 seconds until the participant reports that they are walking at their PWS. Then, in 0.1 mph increments, 1 mph is added to the speed, followed by a decrease at a rate of 0.1 mph every 2‐4 sec until they re-establish their PWS. This procedure will be repeated 3 times in total. The speeds will be averaged to determine their PWS. The PWS assessment will only be performed at baseline. Participants will also be blinded to the digital speed display while walking on the treadmill. Once the PWS has been established, participants will be asked to walk on the treadmill for 5 minutes at their PWS. The treadmill will be used to measure forces during walking, as well as several traditional gait parameters (eg, step time, stride time, and steps per minute in milliseconds). Gait assessment during the follow-up session will be identical, except for determining PWS.

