##### Gait

Secondary outcomes will assess the effects of spinal manipulative therapy on spatiotemporal gait characteristics. Gait will be evaluated using inertial measurement motion capture units and an instrumented force-plate treadmill (Noraxon USA Inc). Spatiotemporal gait parameters will include step length, step time, cadence, and velocity. Gait events will be identified using vertical ground reaction force thresholds implemented within Noraxon’s analytical pipeline. Where applicable, parameters will be processed bilaterally and averaged to generate representative values for each participant. Gait will be evaluated at baseline and at the end of the second session to assess changes over time, as well as differences between participants receiving genuine SMT versus sham SMT.

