### Methods in Analysis to Handle Protocol Nonadherence and Any Statistical Methods to Handle Missing Data

We will report the number and percentages of withdrawals in each of the groups. Based on the trialists’ experience, loss to follow-up is expected to be no more than 15%, which has been factored into our sample size calculation. Regarding secondary outcomes, mixed models have been shown to provide robust estimates in longitudinal designs even with high levels of missing data.

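### The gait mixed model is specified for repeated change scores, but the schedule yields one per participant, so its time and random-intercept terms are not identifiable and its missing-data claim does not hold

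*Protocol article*

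**What the plan says.** Protocol article, Gait: "Gait will be evaluated at baseline and at the end of the second session to assess changes over time". Where applicable, "parameters will be processed bilaterally and averaged to generate representative values for each participant", so left and right sides do not supply replicate rows. Participant Timeline: "This trial will require 2 sessions, one week apart". Assessments: "Gait assessment during the follow-up session will be identical, except for determining PWS". No section shown describes a second post-baseline gait assessment.

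Statistical Considerations (Secondary Outcomes): "mixed models will be run via custom R scripts incorporating the lme4 package", and "Between-group change score differences over time will be evaluated using linear mixed models with random intercepts adjusting for age, sex, and baseline values". The printed `lmer` formula has y minus y_baseline as response, and time*group, y_baseline, age, sex and (1|ID) on the right. The gamma/log-link fallback has the same response and terms. Between-group differences in change, with 95% CIs, are to come from emmeans. The section declares secondary estimates exploratory and rules out significance testing.

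For missing data in the secondary outcomes, the section on nonadherence and missing data relies on the statement that "mixed models have been shown to provide robust estimates in longitudinal designs even with high levels of missing data".

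**The concern.** A random intercept and a time-by-group term need at least two outcome rows per participant. Two gait assessments, one of which is subtracted to form the outcome, leave one row. The article fixes the visits, the formula and the package, so this is a conflict between stated elements and not a detail left to a fuller document.

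The gait results rest on estimation alone, so the confidence interval is the whole result. If the printed model stops when first run, the analyst must choose a replacement with the data in hand, and some replacements give wrong intervals. The only missing-data provision for gait also rests on a property that this model does not have.

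**Working it through.** **Inputs from the protocol article.** Two gait assessments, one averaged value at each (Gait; Assessments). Evaluable n of about 25 per arm, inflated for 15% loss (Sample Size): 25/(1 − 0.15) = 29.4, rounded up to 30 per arm, 60 in total. That reproduces the plan's figure. The plan gives no figure for the gait model itself.

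**Follow-up change scores only (the stated schedule).** With 60 participants there are 60 rows and 60 IDs.
- The fixed part has 7 columns: intercept, time, group, time:group, y_baseline, age, sex. Time is constant, so it is aliased with the intercept, and time:group is aliased with group. The rank is 7 − 2 = 5.
- Each row has variance τ² + σ² and rows are independent, so only the sum can be estimated. On simulated data at N = 60 with total variance fixed, the REML criterion was −84.084913 whether the random intercept took 0, 25, 50, 75 or 99% of it.
- The printed formula run in lme4 on 50 simulated participants stops: the number of levels of the grouping factor must be smaller than the number of observations.
- With that check set to ignore and time coded as a numeric constant, lme4 drops the two aliased columns and reports a singular fit. On one simulated data set of 50 it returned a group effect of 0.3558 (SE 0.2324). Ordinary least squares of change on group, baseline, age and sex gave 0.3558 (SE 0.2324), and so did the same regression on the follow-up value. A one-level factor for time would still have to be removed.

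**Baseline rows kept as change = 0 (not stated in the protocol).** With 50 participants there are 100 rows, the rank is 7 of 7, and `lmer` runs. The added rows are zero by construction.
- In 300 simulations (25 per arm; assumed residual SD 2, true difference 1, baseline slope −0.3) the random-intercept variance was estimated as 0 every time. The mean baseline slope was −0.151, about half the true value. For the follow-up group contrast the mean SE was 0.49 against an empirical SD of 0.61, with 87% coverage. ANCOVA had mean SE 0.59, empirical SD 0.57 and coverage 96%.
- The reason, ignoring covariates: pooling rows of variance s² with rows of variance about 0 gives a residual variance near s²/2. The follow-up contrast is then given variance 2(s²/2)/n = s²/n when the truth is 2s²/n, an SE ratio of 1/√2 = 0.71. Coverage is about P(|Z| < 1.96 × 0.707 = 1.386) = 83%.
- The time:group contrast uses four cells, so its model variance is 4(s²/2)/n = 2s²/n, which is correct. Its coverage is therefore near nominal.

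Coverage by assumed baseline/follow-up correlation r (25 per arm, no true effect, 1,500 trials per setting):

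| r | Follow-up contrast, zero-row layout | ANCOVA |
|---|---|---|
| 0.5 | 0.851 | 0.955 |
| 0.7 | 0.845 | 0.949 |
| 0.9 | 0.862 | 0.955 |
| 0.95 | 0.827 | 0.943 |

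Model SEs for the follow-up contrast were about 0.70–0.74 of the true SD. The time:group coefficient covered about 94–96%, but it equals the unadjusted difference in mean change: the covariates are constant within a participant and cannot affect it. At r = 0.5 its SD was 0.286 against 0.250 for ANCOVA. In large samples the ratio is √(2/(1 + r)): 1.15 at r = 0.5, 1.03 at 0.9, 1.01 at 0.95.

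**Missing data.** At 15% loss, 60 × 0.15 = 9 participants could lack session-2 gait. None would have a change score. In the zero-row layout each would add only a constructed zero.

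**The case against.** A reader might infer that the model cannot be fitted at all unless zero-change baseline rows are added, and hence that the gait intervals will be much too narrow. The documents do not support that. The lme4 stop is a default check that can be switched off. With time numeric, what remains is exactly the ANCOVA group estimate and SE. The plan already adjusts for baseline, age and sex, so on the stated schedule the between-group estimand survives and the fault lies in surplus terms. No section says baseline rows enter as zeros, so the low coverage belongs to a layout that an analyst might choose, not to the plan.

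Within that layout the under-coverage also depends on the contrast. The plan's wording about change differences over time can be read as the interaction, which covers near nominally; an emmeans comparison at follow-up would be the affected one. The precision lost with the interaction is small if r is high. That is plausible, because preferred walking speed is set once at baseline and reused, but the protocol gives no value for r.

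Finally, gait is secondary and exploratory, and the first symptom would be a visible error. These points limit the weight. They do not rescue the printed formula, or the missing-data statement, which cites a general property of longitudinal mixed models that a single change score does not share. Figure 1 is not shown; a further gait visit there would conflict with the Gait section and would need reconciling.

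**Conclusion.** The gait model is wrong as written, with moderate severity. On the stated schedule, time, time:group and the random-intercept variance are not identifiable. By default lme4 refuses the model; overridden, with time numeric, it reduces to ANCOVA without bias or loss.

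The 83–86% coverage is conditional on three things: the unstated zero-row layout, the follow-up contrast, and the simulation settings (25 per arm, r of 0.5–0.95). It shows what an improvised repair could cost and does not predict the trial's results. The missing-data conclusion depends on none of these settings. The Bang BI analysis and the sample size are unaffected.

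**What to change.** Replace the printed model with `lm(y_followup ~ group + y_baseline + age + sex)`, report the group coefficient with its 95% CI, and delete the missing-data robustness statement in both places where it appears.

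If participants with only a baseline assessment should contribute, model raw y at both visits with time, time:group, a common baseline mean for the two arms and a random intercept. Leave y_baseline out as a covariate, and do not use the change score as response.

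Revise the gamma fallback too: it repeats the same terms and response, and a gamma model does not accept the zero or negative values that a change score can take.

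The cost is a wording change and a simpler analysis script, with no effect on data collection or participants. It is best made before the gait data are analysed, so that the replacement is not chosen after seeing them.

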### Strengths and Limitations

One potential limitation of our protocol is that we are not undertaking a crossover design. By limiting participants to one study arm, they will not receive both genuine and sham SMT, therefore not controlling for between-subject variability. However, since manual therapies may have long-lasting neurophysiological effects [32], a parallel study can avoid carryover effects. When it comes to gait, there is a high variability due to individual differences, which we will account for using a generalized linear mixed model. Another potential limitation relates to our recruitment of participants from a geographic area with a population that is more familiar with chiropractic care due to the local chiropractic college. We will exclude participants with substantial chiropractic education to help mitigate this potential bias.

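### The fallback gait model applies a gamma family with log link to change scores, which can be zero or negative, so as written it stops with an error unless every analysed change is positive

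*Protocol article*

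**What the plan says.** In the protocol article, Statistical Considerations (Secondary Outcomes), the gait analysis is set on the change scale: "Between-group change score differences over time will be evaluated using linear mixed models with random intercepts adjusting for age, sex, and baseline values". The contingency follows: if the assumptions of that model fail badly, the analysis moves to "generalized linear mixed models incorporating a gamma distribution and a log link".

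Both models are printed as formulas. The glmer formula has the same left-hand side as the lmer formula, follow-up value minus baseline value. It also has the same right-hand side: time by group, baseline, age, sex and a random intercept per participant. Only the family and link differ. The article mentions no shift, no transformation and no return to the raw measurement.

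The reporting sentence is: "Between-group change score difference point estimates and 95% CIs will be computed and plotted using the emmeans package".

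The Gait section lists the outcomes: "Spatiotemporal gait parameters will include step length, step time, cadence, and velocity". It schedules gait at baseline and at the end of the second session, so there is one post-baseline value per participant. The Assessments section determines preferred walking speed at baseline only and otherwise repeats the treadmill walk unchanged.

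**The concern.** A gamma model describes strictly positive quantities. Raw step length, step time, cadence and velocity are such quantities, but their changes from baseline are not. The remedy named for a failed linear model is therefore one that these data will very probably not allow.

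If the contingency arises, the analyst has three ways forward:

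- discard participants whose value did not increase, which selects on the outcome;
- add a constant, whose size is arbitrary and affects the estimate;
- choose another method after seeing the data.

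Each undoes the purpose of naming a fallback in advance. There is also a mismatch of scale. With a log link, group contrasts are ratios of mean change on the model scale, while the article promises differences in change.

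**Working it through.** **Inputs from the article.** The response (change), family (gamma) and link (log) come from Statistical Considerations (Secondary Outcomes). The gait schedule comes from Gait, and the fixed walking speed from Assessments. Sample Size gives 25 evaluable participants per arm, inflated for 15% loss: 25 / (1 − 0.15) = 29.4, rounded to 30, which reproduces the article's figure. Hence n = 50 evaluable and n = 60 randomised.

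**Step 1: support of the distribution.** For shape k and scale θ, the gamma log-density is (k − 1) log y − y/θ − k log θ − log Γ(k). The term log y is undefined for y < 0 and infinite at y = 0. R's gamma family checks for this and stops if any response is zero or below.

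**Step 2: test fits on simulated changes (n = 50).** With the mean change at 0, 0.5 and 1 SD, 24, 15 and 7 of the 50 values were non-positive. A gamma model with log link stopped each time with `non-positive values not allowed for the 'Gamma' family`. A glmer fit with the article's terms, less age and sex, gave the same error with baseline rows kept. So did a fit to follow-up rows only, with the time terms dropped.

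**Step 3: the two possible data layouts.**

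- Baseline rows kept: their change is y_baseline − y_baseline = 0 for everyone, so failure is certain.
- Follow-up rows only: the model can be fitted only if every participant's change exceeds zero.

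The article does not say which layout is meant.

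**Step 4: chance that all changes are positive, follow-up rows only.** Assume independent normal changes with mean μ and SD σ. Then P(all > 0) = Φ(μ/σ)^n, and the expected number of non-positive changes is n[1 − Φ(μ/σ)]. The article gives neither μ nor σ, so the ratio is varied.

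| Assumed μ/σ | P(all > 0), n = 50 | Expected non-positive, n = 50 | P(all > 0), n = 60 |
|---|---|---|---|
| 0 | 0.5^50 = 9e-16 | 25 | 9e-19 |
| 0.5 | 0.6915^50 = 1e-8 | 15.4 | 2e-10 |
| 1 | 0.8413^50 = 0.0002 | 7.9 | 0.00003 |
| 2 | 0.9772^50 = 0.32 | 1.1 | 0.25 |

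**Step 5: a check that needs no distribution.** Cadence is the reciprocal of mean step time, apart from units. If one rises in a participant, the other falls. At a fixed belt speed, step length is speed times step time, so step length and cadence also move in opposite directions. The fallback therefore cannot be fitted both to cadence and to step time or step length. Velocity change should sit at or near zero, because the belt speed is carried over from baseline.

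**The case against.** The strongest reply is about weight. The article calls its secondary estimates exploratory and limits them to estimation without significance tests. The gamma model is used only if the linear model badly fails its checks. The primary Bang index, its sample size and the James index do not depend on it. The likely failure is also a visible software error, not a silently wrong answer. All of this stands, and it limits the severity.

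A second reply is that the probabilities assume normal changes, although the fallback may be triggered by non-normality, and that the mean-to-SD ratios are not from the article. This also stands. The table is an illustration; the argument rests on Steps 1, 3 and 5.

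Three stronger readings are tempting, and the article does not support them.

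- A reader might infer that the participants lost would be those who got worse. No direction of benefit is defined for any gait parameter, so one can say only that they are those whose value did not increase.
- A reader might take the Strengths and Limitations remark that "there is a high variability due to individual differences, which we will account for using a generalized linear mixed model" as making the gamma model the main gait analysis. It names no gamma family, log link or change score. Its difference from the linear-first plan is a separate matter.
- A reader might conclude that baseline rows make failure certain. That holds only if those rows are in the analysis data, which the article does not state.

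**Conclusion.** The point holds. The fallback is fixed wrongly in the printed formula, so this is neither loose wording nor detail left to an analysis plan. It cannot be fitted once any analysed change is zero or negative. Under the assumed normal changes with n = 50, it could be fitted with probability about 9e-16 at no mean change, and still only about 0.32 at a mean change of 2 SD. At no mean change, forcing a fit by exclusion would discard about 25 of 50 participants.

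The scope is narrow: a conditional fallback for exploratory gait outcomes. The blinding results are unaffected. It should be fixed, but it does not threaten the trial's main conclusion.

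**What to change.** Replace the fallback with a model that can be estimated. There are two options.

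(a) **Keep the stated estimand.** Regress change at follow-up on group, baseline value, age and sex. Give bootstrap or heteroscedasticity-robust 95% CIs for the between-group change score difference. The reporting sentence can stay.

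(b) **Move the gamma model to the raw scale.** Fit the strictly positive follow-up value on group, log(baseline), age and sex with a gamma family and log link. State that the result is a ratio of means, or a back-transformed difference of marginal means, and amend the emmeans sentence to match.

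Under either option, state that the time-by-group term and the participant random intercept are dropped, and why: the Gait section provides one post-baseline value per participant, so neither can be estimated from follow-up rows alone. Neither option makes velocity informative if the belt speed is simply repeated.

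The cost is a revised formula and reporting sentence and, under (b), a different effect measure from the linear model. Option (a) is the simpler because it leaves the estimand alone. Analysis is projected for Fall 2026, so the change can be made and declared beforehand.
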